**Methods:**

A total of 92 schools are randomised to intervention and control group in Kerala. A baseline survey was conducted in all schools to assess the prevalence of hypertension and its risk factors among school teachers in Thiruvananthapuram district of Kerala state, India. Teachers in both sets of schools will receive a leaflet containing details on the importance of controlling hypertension. With the objective of improving control of hypertension, the intervention schools will additionally receive self-management education and behavioural intervention programs delivered by trained intervention managers along with measurement of weight, waist circumference and blood pressure. This intervention program will be developed based on the findings of the baseline survey and selected components of successful models of hypertension control from previous research done in similar settings. The intervention will be given for 3 months after which a post-survey will be conducted among teachers of both control and intervention schools. The primary outcome is change in control of hypertension and secondary outcome is the change in behavioural risk factors of hypertension both in the control and intervention groups.

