### Study sample

Government or government-aided schools in Thiruvananthapuram district were identified as the primary sampling unit. The sample size for the baseline survey was 2200 teachers, expecting the prevalence of hypertension as 30% [14] to get a 95% confidence interval with an absolute precision of 2.5%, for an assumed design effect of 1.5 and non-response rate of 10%. The sample size was calculated using the Open Epi software. Among the total of 999 schools in the revenue district of Thiruvananthapuram, 902 are government or government-aided private schools. Of the 902 schools, we randomly selected 92 schools for the baseline survey using a computer-generated random assignment to get 2200 school teachers for the baseline survey (see Fig. 1). From each chosen school, we selected 15 teachers randomly if there were 15–55 teachers and for every additional 50 teachers, we selected another15 teachers. For schools with < 15 teachers, all teachers were selected. So, each cluster has approximately 15 teachers. The schools will be identified for the intervention and control by stratified randomisation with the number of hypertensives as the stratification variable.

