### Outcome measurements

Prevalence, awareness, treatment and control of hypertension along with other risk factors of hypertension are collected during the baseline survey. The newly diagnosed hypertensives in the baseline survey were asked to visit their regular doctor or the nearest government primary health centre/hospital for confirmation of hypertension and management. The primary outcome of the study will be control of hypertension (defined as SBP < 140 mmHg and DBP < 90 mm [28]). This will be compared between intervention and control groups after 3 months of intervention. We will also compare the difference in mean systolic and mean diastolic blood pressure at baseline and post intervention period for control and intervention group. Secondary outcomes will be awareness and treatment rates for hypertension among teachers of intervention and control groups. We will also assess the change in risk factors of hypertension such as tobacco, alcohol, physical inactivity, unhealthy diet and, overweight/obesity after the intervention in the intervention group and the control group.

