### Plan for data collection and analysis

A follow-up survey will be conducted after the intervention to assess the change in control of hypertension, awareness and treatment for hypertension as well as other risk factors of hypertension both in control and intervention groups. Baseline survey data will be analysed to evaluate the prevalence of hypertension, and other behavioural risk factors of hypertension. Medication adherence will also be assessed. The quality of life will be analysed with hypertension status. Analysis of the opinion among school teachers regarding the feasibility of intervention options will also be done. Based on these results and already reported intervention programs in the state we will develop interventions suitable for school teachers on controlling hypertension. We will compare the control of hypertension in both study groups with the findings from baseline and post survey.

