### Data management and statistical analysis

All assessments and data forms will be completed in real time on the day of measurement. Edit checks will be performed and data verified as necessary. Access to data will be restricted to the leading researchers. Hard copies of data will be stored in a secure place of storage while soft data will be stored securely using file locks and passwords. All identifiable information will be stored in a separate database from the other data. Data will be stored for 5 years after completion of the project. We will use intention-to-treat analysis for comparing the change in control of hypertension both among intervention and control groups.

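### The primary outcome is worded both as a change in control and as control after 3 months, and mean BP is compared as a baseline-to-post difference instead of being adjusted for baseline

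*Protocol article*

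**What the plan says.** Four places in the Protocol article describe the main comparison.

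- Abstract, Methods: "The primary outcome is change in control of hypertension and secondary outcome is the change in behavioural risk factors of hypertension".
- Outcome measurements: "The primary outcome of the study will be control of hypertension (defined as SBP < 140 mmHg and DBP < 90 mm [28", followed by "This will be compared between intervention and control groups after 3 months of intervention".
- Plan for data collection and analysis: "We will compare the control of hypertension in both study groups with the findings from baseline and post survey".
- Data management and statistical analysis: "We will use intention-to-treat analysis for comparing the change in control of hypertension both among intervention and control groups".

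For mean SBP and DBP, Outcome measurements adds that the team will "compare the difference in mean systolic and mean diastolic blood pressure at baseline and post intervention period" for the two arms.

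The baseline survey precedes randomisation (Study design), and schools are stratified by their number of hypertensives (Study sample). Baseline BP and control status are therefore available as pre-randomisation covariates. The article does not mention baseline adjustment.

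**The concern.** The abstract and the statistical analysis section name a change. Outcome measurements, which defines the variable, names a level at follow-up. Plan for data collection and analysis uses both surveys without saying how. Computed on the same data, a difference in changes and a difference in follow-up levels will generally give different estimates, standard errors and p-values. With both in print, either could be called the planned primary once results are known.

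The BP sentence raises a separate question of efficiency. Subtracting a baseline value gives it a fixed weight of one, whereas adjusting for it lets the data set the weight. Because the baseline is already collected, the lost precision would be avoidable.

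**Working it through.** **The plan's own figure.** The only sample size given is for the prevalence survey: "The sample size for the baseline survey was 2200 teachers, expecting the prevalence of hypertension as 30"%, with precision 2.5%, design effect 1.5 and non-response 10% (Study sample).

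- 1.96² × 0.3 × 0.7 / 0.025² = 1290.7
- 1290.7 × 1.5 = 1936.1
- 1936.1 / 0.9 = 2152 rounded up, within 3% of 2200

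The figure reproduces, but it has no bearing on the between-arm contrast. The article gives no effect size, SD, power or baseline-to-follow-up correlation for that contrast.

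**Do the two versions of the primary differ?** Let p0 and p1 be the proportions controlled at baseline and follow-up, in arms I and C.

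- Difference in changes: (p1I − p0I) − (p1C − p0C) = (p1I − p1C) − (p0I − p0C).
- Randomisation makes the expected value of (p0I − p0C) zero, so both versions target p1I − p1C.
- In any one trial (p0I − p0C) is not exactly zero. The change version subtracts all of it and the level version none.
- Off the absolute scale the targets separate. For example, a ratio of changes, (p1I − p0)/(p1C − p0), is not the ratio of levels p1I/p1C. The article fixes no scale.

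An illustration for the binary primary, ignoring clustering, takes 13% controlled at baseline (the recent Kerala figure in Background), an assumed 25% at follow-up and an assumed within-person correlation r. The variances are 0.13 × 0.87 = 0.1131 and 0.25 × 0.75 = 0.1875, and the product of the SDs is √(0.1131 × 0.1875) = 0.1456.

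| r | level: 0.1875 | change: 0.3006 − 2r(0.1456) | adjusted: 0.1875(1 − r²) | change/level | change/adjusted |
|---|---|---|---|---|---|
| 0.3 | 0.1875 | 0.2132 | 0.1706 | 1.14 | 1.25 |
| 0.5 | 0.1875 | 0.1550 | 0.1406 | 0.83 | 1.10 |

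Which printed version is the more precise depends on a correlation that nobody has stated. The adjusted comparison is the most precise in both rows.

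**Mean SBP and DBP.** With equal variance s² at both surveys and correlation r, the relative variances of the randomised contrast are:

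- follow-up only: s²
- change score: 2(1 − r)s²
- baseline-adjusted (ANCOVA): (1 − r²)s²
- ANCOVA/change = (1 + r)/2, so change/ANCOVA = 2/(1 + r)

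| assumed r | follow-up only | change | ANCOVA | change/ANCOVA | SE ratio |
|---|---|---|---|---|---|
| 0.3 | 1 | 1.40 | 0.91 | 1.54 | 1.24 |
| 0.5 | 1 | 1.00 | 0.75 | 1.33 | 1.15 |
| 0.6 | 1 | 0.80 | 0.64 | 1.25 | 1.12 |
| 0.7 | 1 | 0.60 | 0.51 | 1.18 | 1.08 |
| 0.8 | 1 | 0.40 | 0.36 | 1.11 | 1.05 |

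**Check with clustering.** A simulation used 92 schools, an assumed 7 hypertensives per school (2200 × 0.3 / 92 = 7.2), an assumed SD of 15 and ICC of 0.03, and school-level analysis. Standard errors for follow-up only / change / adjusted were:

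- r = 0.3: 1.29 / 1.52 / 1.23
- r = 0.5: 1.28 / 1.28 / 1.11
- r = 0.7: 1.29 / 0.99 / 0.93

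The change/adjusted variance ratios were 1.52, 1.33 and 1.14, close to the formula's 1.54, 1.33 and 1.18.

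**The case against.** The best defence is that Outcome measurements is the defining section. It gives the definition, the time point and the contrast, and the word change elsewhere may be shorthand for it. Randomisation after the baseline survey gives both wordings the same absolute risk difference. The BP sentence is loose: it states no model and could even mean before-after comparison within each arm. A condensed article may leave covariates to a fuller document that is not shown.

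Much of this stands. The absence of a stated adjustment is not a fault in itself, and the article does not rule adjustment out. However, the shorthand reading is hard to sustain when the only sentence on inferential analysis applies intention-to-treat to the change. An unseen analysis plan could choose one version, but the published sections would still disagree. The within-arm reading of the BP sentence would be weaker than a change score, because it does not compare the arms.

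A reader might infer four stronger things that the documents do not support:

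- **That the two wordings are different estimands on every scale.** On the absolute scale they are not.
- **That the precision loss computed for mean BP applies to the primary.** The formula is for a continuous outcome with equal variances, and mean BP is introduced as an additional comparison.
- **That regression to the mean biases the result.** It is expected equally in both randomised arms. It distorts within-arm change and matters between arms only through chance baseline imbalance, which stratification by number of hypertensives partly limits.
- **That the long gap in Trial status means r below 0.5, so that a change score is worse than ignoring baseline.** Nothing in the article links the interval to a correlation, and August 2019 is when results are expected, not the date of the follow-up survey.

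**Conclusion.** The point holds in two parts of unequal weight.

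The firmer part is the inconsistent primary. The article prints a change and a post-intervention level, and in one section names no contrast. The difference lies in the estimator, its standard error, its response to chance imbalance and, off the absolute scale, the quantity itself. That is enough to leave a choice after the data are seen.

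The second part concerns efficiency for mean SBP and DBP only. It rests on reading the BP sentence as a change score, on equal variances at the two surveys and on an assumed r. Over r from 0.3 to 0.8 the change score carries about 54% down to 11% more variance than the baseline-adjusted comparison (SE about 24% down to 5% larger). The loss is modest if r is high.

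The binary illustration shows that the choice matters for the primary too, but it rests on assumed inputs and is not an estimate of the loss in this trial.

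**What to change.** Make the abstract, Outcome measurements, Plan for data collection and analysis, and Data management and statistical analysis state one primary, and name the effect scale. A suitable form is the proportion controlled (by the article's own BP definition) at the post-survey, intervention versus control, among teachers hypertensive at baseline. It should come from a model that adjusts for baseline BP or baseline control status and for the stratification variable, and that accounts for clustering by school. One form of baseline adjustment is enough: among hypertensives, control status follows from the baseline pressures, so entering both is largely redundant. Naming the population is part of a complete definition.

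Replace the BP sentence with one saying that follow-up SBP and DBP will each be compared between arms, adjusted for own baseline, in the same clustered framework. Report within-arm baseline-to-post change as descriptive only.

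The cost is wording and one covariate-adjusted model. No further data are needed and nothing changes for participants.

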### Blinding

The allocation of sequence, enrolment of participants, and assignment of participants to interventions will be done by a senior statistician based at the implementing institute. The allocation of participants in the intervention group or the control group will be blinded to the outcome assessors. Since this is a behavioural intervention trial, blinding cannot be applied to the persons delivering the intervention.

### Plan for data collection and analysis

A follow-up survey will be conducted after the intervention to assess the change in control of hypertension, awareness and treatment for hypertension as well as other risk factors of hypertension both in control and intervention groups. Baseline survey data will be analysed to evaluate the prevalence of hypertension, and other behavioural risk factors of hypertension. Medication adherence will also be assessed. The quality of life will be analysed with hypertension status. Analysis of the opinion among school teachers regarding the feasibility of intervention options will also be done. Based on these results and already reported intervention programs in the state we will develop interventions suitable for school teachers on controlling hypertension. We will compare the control of hypertension in both study groups with the findings from baseline and post survey.

### Intervention components

Based on the findings of the baseline survey and findings from earlier research in the state, we will prepare the content of the intervention for improving the control of hypertension for school teachers. Also, selected component of successful models on risk factors of non-communicable diseases including hypertension, from previous research done in the state, which showed improvement in control of hypertension [8], will be incorporated into the intervention program. We will also take the relevant components from similar NCD prevention frameworks done in the state [14]. The intervention session will be designed with self-management education and research team supported intervention. Monitoring of blood pressure was reported to improve blood pressure control in a randomised trial among hypertensive patients in North Carolina [29]. Since we took the schools as the unit of randomisation, all teachers in the intervention schools will receive the intervention. We have gathered details from selected schools to know the feasibility of the intervention to improve hypertension control. Based on these findings, we will design a workable intervention program for school teachers in this community.

A multi-component intervention program will be implemented in intervention schools. Teachers in the intervention schools will receive educational intervention on lifestyle modification including healthy diet habits, importance of physical activity, tobacco and alcohol cessation programs and awareness, control and treatment of hypertension and the importance of medication adherence on hypertension. During the intervention period, all the schools in the intervention group will receive the above education components once every 2 weeks for a period of 3 months. Thus, each school will receive six such sessions. In these sessions, educational materials including healthy lifestyle practices for hypertension control will be given to all teachers in the intervention group. Health education classes including power point presentation, educational videos and interactive discussions will be part of these sessions at schools. All these sessions will be given as a group activity in each of the intervention schools. During these sessions, attention will also be given to the pre-hypertensives identified in the baseline survey. This would help to reduce the progression rate from pre-hypertension to hypertension and is also likely to reduce the incidence of hypertension.

In each of these meetings, weight and waist circumference will be measured along with blood pressure for all teachers who participated in the baseline survey and the values will be communicated to them. Questions on medication for hypertension and health care visit for high blood pressure during the last 2 weeks will also be asked to hypertensive teachers and responses will be noted. These intervention sessions will be face-to-face with the objective to motivate school teachers to increase the control rate of hypertension. During the intervention period, the development of changes in other risk factor behavioural characteristics will be monitored, and the sessions will help to overcome barriers and difficulties to control hypertension. Trained health educators, researchers and public health experts will handle the intervention components.

A WhatsApp group will be formed for those with hypertension identified during the baseline survey, and relevant educational materials and information will be regularly shared through the WhatsApp message system. Regular short message service (SMS) will be sent to those in the hypertension group as a reminder to take medication and keep healthy lifestyle practices for control of hypertension. Regular monitoring of blood pressure will be insisted on by messages through this smart-phone based intervention. The fidelity of the WhatsApp intervention will be ensured by contacting a sample of the participants over phone and finding out whether they received the Whatsapp message and if they received what was the message and what did they do about that. The intervention will be delivered for 3 months.

### Control group

During the baseline survey, all teachers who participated in this study are informed about their blood pressure, weight, height and waist circumference measurements. Those who are identified as hypertensives (SBP > =140 mmHg or DBP > =90 mmHg) during the survey are advised to check their blood pressure again for further confirmation and management. At the end of the baseline survey, all teachers participated in this study are provided educational material on hypertension and its risk factors. No other intervention will be given to the control group during the intervention period.

### Data management and statistical analysis

All assessments and data forms will be completed in real time on the day of measurement. Edit checks will be performed and data verified as necessary. Access to data will be restricted to the leading researchers. Hard copies of data will be stored in a secure place of storage while soft data will be stored securely using file locks and passwords. All identifiable information will be stored in a separate database from the other data. Data will be stored for 5 years after completion of the project. We will use intention-to-treat analysis for comparing the change in control of hypertension both among intervention and control groups.

### Trial registration

This trial was registered with the Clinical Trials Registry of India (CTRI) prospectively on 18th January 2018 [CTRI/2018/01/011402]. We started recruiting participants after the registration number has been received.

### Dissemination

Each participant is assigned a unique identification number after the baseline survey. Opportunities for active dissemination of findings will be pursued throughout the study by submission for presentation at national and international conferences and through publication in peer-reviewed national and international journals. The overall study results will be disseminated to participating schools. The details of the intervention program will also be communicated through publications to understand the details of the efficacy trial of control of hypertension among school teachers. After the post-survey, the comparative findings on control of hypertension will be disseminated for both control and intervention group. The funding agency will also be informed of the findings of the study. Findings will also be shared with the Department of Education, Government of Kerala.

## Discussion

Comprehensive estimation of the efficacy of the behavioural intervention for control of hypertension among school teachers is the first of its kind in India. Healthy teachers provide continuity and stability so essential for educational success. Also, Kerala state in India is having the highest level of education and has reported a high prevalence of hypertension [10]. The findings of the present study are likely to be an upper estimate of the level of efficacy of the behavioural intervention in control of hypertension in India. A short intervention period of 3months was a limitation of the study. However similar short intervention studies to improve hypertension control was reported earlier [23].

There is limited evidence on the efficacy of educational intervention with regular monitoring of blood pressure for improving control of hypertension in India. The intervention will improve the awareness of hypertension control and other risk factors like tobacco use, alcohol consumption, physical inactivity and unhealthy diet. It also brings awareness of the importance of taking regular medication for controlling hypertension. This intervention program will incorporate the previous experience of hypertension control programs conducted in similar settings [8]. We have done a formative research among school teachers to assess the possible components of intervention. The program is expected to increase their awareness on lifestyle risk factors which are also beneficial to the community irrespective of the trial outcome, which is another strength of the study. A meticulous randomisation process followed in this study is another strength which allows comparison, statistical reliability and minimises biases as well as confounding factors, which is the strongest possible analysis of the effect of an intervention. The randomisation followed in this study mitigates major operational biases.

In particular, we have shown that this intervention is applicable across very diverse rural settings, so there is considerable potential to implement and scale up across rural India and potentially other resource-poor regions in other countries. Future programs, incorporating comprehensive collection of data such as changes in medication use, changes to lifestyle behaviours, and knowledge of hypertension may help tease out which factors are best targeted to improve the control of hypertension in these settings, if successful, for scale up and implementation among similar groups and educational settings.

This study is likely to have an impact not only on teachers but also on students and their family members indirectly. If this intervention is found to be effective, the findings will provide a practical approach towards control of hypertension and other non-communicable diseases and their risk factors among school teachers in a similar setting. Also, comprehensive collection of data on behavioural life style changes in this study would help to prioritise the risk factors for control of hypertension. We also hypothesize that an intervention among school teachers would provide a higher level of impact of such an intervention program on control of hypertension. If such an intervention is successful among school teachers, it opens the way for scale up and implementation among similar groups and educational settings to achieve adequate control of hypertension in a cost-effective way. These findings will have important implications in the medical and public health field in controlling hypertension.

